### Outcome measurements

The time points for all outcomes are at baseline and at 1, 2, 3, 4, 5, and 6 months postmenstrual cycles.

#### Primary outcome

The primary outcome is the mean menstrual pain intensity change measured by visual analog scale (VAS) from baseline to 6 months. The VAS is a valid and reliable tool that has been widely used in various clinical trials involving patients with PD [27]. Participants will be asked to indicate a perception of pain intensity scored from 0 to 100 (0, no pain; 100, maximum).

#### Secondary outcomes

The secondary outcomes are (1) the change of the mean Cox Menstrual Symptom Scale (CMSS) score from baseline to 6 months, (2) the change of the mean Self-rating Depression Scale (SDS) [28] score from baseline to 6 months, (3) the change of the mean Self-rating Anxiety Scale (SAS) [29] score from baseline to 6 months, and (4) the change in the proportion of the TCM syndrome scale score from baseline to 6 months. The CMSS is a compact questionnaire for the evaluation of menstrual pain symptoms [30]. It consists of 18 items, each of which is divided into five levels according to the severity of symptoms (a score of 0 indicates no discomfort; 1 for mild discomfort; 2 for moderate discomfort; 3 for severe discomfort; and 4 for extremely severe), including an evaluation of the general frequency and average severity of menstrual symptoms [31]. The SAS and SDS are scoring tools for depression and anxiety disorders, respectively, and are widely used in clinical PD patients because of the emotional changes that often accompany PD. The SAS questionnaire for self-rated includes 20 items, and each is answered on a 4-point scale ranging from 0 (no time) to 4 (most of the time), with a total score of more than 40 indicating a clinically relevant anxiety disorder [32]. The higher the score, the more severe the anxiety. The SDS is a self-rated scale for evaluating the severity of depression. The statistical indicators of SAS include 20 questions with a total score ranging from 20 to 80. A score above 40 indicates depressive symptoms, and the higher the score, the more pronounced the tendency to depression [33]. The TCM syndrome scale is a questionnaire for the evaluation of TCM symptoms. It includes 9 items with a total score ranging from 0 to 26, and the higher the score, the more serious the degree of TCM syndrome [34]. The assessments will be performed in a separate space in the outpatient department. All of the outcome assessors will be trained in conducting interviews and performing measurements before the study.

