### Sample size

The sample size estimation was based on the mean difference in the change of the menstrual pain intensity from baseline. Based on previous studies and our pilot trial, we made the following assumptions in calculating the sample size: a mean difference of 1 between two groups, SD of total score of 1.67, a ratio of 1:1 between the two groups, a two-sided significance level of 0.025 and a power of 0.9 [35, 36]. With these assumptions, a minimum sample size of 116 patients (58 patients in each group) is needed. Considering an estimated 10% dropout rate, the estimated sample size was 128 patients (64 patients per group).

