### Data analysis

At the end of all measurements’ data collection, a skilled statistician blinded to group allocation will be performed by SPSS Statistics for Windows, version 22.0 (SPSSInc., Chicago, III., USA). We will descriptively summarize patient characteristics, outcome variables, and adverse events. Continuous variables, such as age and disease course, will be presented as mean ± standard deviation (*SD*) and analyzed by an independent-sample *T*-test. Quantitative variables such as baseline variables of socio-demographic data will be analyzed using *χ*^2^ or Mann-Whitney *U* tests. The repeated measurement variables, such as the primary and second outcomes, are analyzed by repeated-measures analysis of variance (ANOVA) or generalized estimation equations (GEE).

Both the full analysis set (FAS) and the per-protocol analysis set (PPS) will be used simultaneously to evaluate the effect and safety of GFW for PD. The FAS is for all participants who complete randomization and are assigned to receive treatment. The PPS is for the individuals who receive the assigned treatment according to the protocol and complete the entire study. For missing data, we will use the last-observation-carried-forward method. Although no interim analysis of outcomes is planned, a summary of the enrolment progress, AEs, and protocol deviations will be provided to the data monitoring committee (DMC) members. The trial should be terminated if there is clear evidence that SAEs are associated with the intervention or develop a serious illness. Statistical significance will be set at *P* < 0.05.

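### The TCM syndrome outcome is worded as a change in a proportion, which fits several different variables, and no baseline adjustment is named for it

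*Protocol article*

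**What the plan says.** The Secondary outcomes section lists four scales. For the Cox Menstrual Symptom Scale the outcome is "the change of the mean Cox Menstrual Symptom Scale (CMSS) score from baseline to 6 months", and SDS and SAS are worded in the same way. The fourth outcome is "the change in the proportion of the TCM syndrome scale score from baseline to 6 months".

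The same section describes the TCM syndrome scale as a conventional sum score: "It includes 9 items with a total score ranging from 0 to 26", with higher values meaning a worse syndrome. It does not say what the proportion is of, and it gives neither a percentage formula nor a responder cut-off. The abstract lists only the scale.

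The Data analysis section says that repeated measurements, including the primary and secondary outcomes, "are analyzed by repeated-measures analysis of variance (ANOVA) or generalized estimation equations (GEE". It names no baseline covariate for any of them.

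**The concern.** Three scales are defined on one metric and the fourth on another, although all four are sum scores. Read literally, the TCM wording fits at least three variables:

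- the percentage change of each woman's score from her own baseline;
- the share of women who reach some reduction;
- the score as a share of its maximum, 26.

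These differ in type (continuous or binary), in the model they need and in what they estimate. If the choice were made after the data are seen, it could follow the result, on the scale that measures the syndrome defining the trial population.

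Percentage change also weights women unevenly. A fall of 2 points is 2/4 = 50% from a baseline of 4, but 2/16 = 12.5% from a baseline of 16. Like raw change, it does not use the baseline score efficiently.

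**Working it through.** **Inputs from the article.** Scale range 0 to 26; 58 women per arm before the dropout allowance (Sample size); significance at 0.05 (Data analysis). The planning figures there ("a mean difference of 1 between two groups" and "SD of total score of 1.67") belong to pain intensity, not to this scale. There is no stated power figure for the TCM scale to reproduce.

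**Assumed inputs.** Baseline mean, SD, baseline-to-follow-up correlation ρ and treatment effect, varied as shown below.

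**Step 1: score/26.** Dividing every score by 26 divides the difference and its standard error by 26. The test statistic is unchanged, so this reading has no effect on power.

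**Step 2: what baseline adjustment is worth.** With SD σ at both times, the variance of raw change is 2σ²(1 − ρ), and the residual variance of the follow-up score given baseline is σ²(1 − ρ²). Power is about Φ(difference/SE − 1.96), with SE = √(variance × 2/58). For a difference of 2 points, σ = 4 and ρ = 0.5:

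- Raw change: variance 16, SE 0.743, 2/0.743 = 2.69, power 77%.
- Adjusted score: variance 12, SE 0.643, 2/0.643 = 3.11, power 87%.

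The same formulas give 62% and 81% at ρ = 0.3, and 94% and 96% at ρ = 0.7.

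**Step 3: simulation A, additive effect.** 58 per arm, two-sided 0.05, true difference 2 points, baseline mean 12 to 16, a common 30% improvement in both arms, scores rounded and limited to 0 to 26, baseline at least 3.

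| Assumption | Adjusted score | Percentage change | Raw change |
|---|---|---|---|
| SD 4, ρ 0.3 | 77–80% | 63–68% | 59–61% |
| SD 4, ρ 0.5 | 86–87% | 79–82% | 75–76% |
| SD 4, ρ 0.7 | 96% | 94% | 93% |
| SD 5 | 68–69% | 58–60% | 55–56% |

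Percentage change matched or beat raw change in all 12 scenarios. Repeating the simulation gave overall ranges of 67–96%, 57–94% and 55–93%. The gap to the adjusted score is therefore at least as large for raw change, the metric worded for CMSS, SDS and SAS.

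**Step 4: simulation B, wider inputs.** 4,000 runs per scenario, baseline mean 10 to 16, SD 3 or 4, baseline at least 1, and a 30% reduction as an assumed responder cut-off.

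*Additive effect* of 0.55 × σ√(1 − ρ²), ρ 0.3 to 0.7, 12 scenarios:

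- The adjusted score had 80–83% power and percentage change 54–80%.
- The smallest loss was 82.7 − 79.9 = 2.8 points (mean 13, SD 3, ρ 0.7). The largest was 81.4 − 54.1 = 27.3 points (mean 10, SD 4, ρ 0.3).
- Percentage change beat raw change in 10 of the 12. It was worse by 65.3 − 64.0 = 1.3 points (mean 13, SD 4, ρ 0.3) and by 59.6 − 54.1 = 5.5 points (mean 10, SD 4, ρ 0.3).

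*Effect and error proportional to baseline* (follow-up = baseline × ratio, ratio mean 0.75 and SD 0.25, lowered by 0.14 on treatment), 4 scenarios:

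- Percentage change had 83–86% power and the adjusted score 79–84%, so percentage change gained about 2 to 5 points. A further run of this type gave 2 to 6.
- With a proportional effect but constant error variance, percentage change was again weaker than the adjusted score throughout.

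*Responder share:* 54–67% power, below the adjusted score in all 16 scenarios. The smallest gap was 78.7 − 64.5 = 14.2 points and the largest 81.4 − 53.7 = 27.7 points.

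**The case against.** The strongest objection concerns cause. A comparison of unadjusted percentage change with a baseline-adjusted score changes two things at once. When unadjusted raw change is added, percentage change does no worse than raw change throughout simulation A and in 10 of 12 additive scenarios in simulation B. A reader might infer that the proportion itself makes the outcome less powerful than its sibling scales; the calculations do not support that as a general statement. The distortion from low baselines shows clearly in only one scenario, with a mean of 10 and weak correlation. This objection stands.

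The sign of the difference also depends on the data model, and the article supplies no input for one. That stands too, so no single power loss can be quoted.

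Two further inferences are tempting and should not be drawn. One is that the planned methods cannot handle a proportion: the article offers GEE as an alternative, and GEE accepts binary and proportional outcomes. The other is that percentage change would often be undefined: a baseline of 0 is unlikely, because entry requires the syndrome as diagnosed by two TCM gynecologists.

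Finally, a condensed article may leave a formula or cut-off to the full protocol or SAP. That is fair as to missing detail. It does not answer the wording itself, which fixes a different and ambiguous metric for one of four scales.

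**Conclusion.** The point holds as one of definition and analysis choice. The TCM outcome is worded unlike CMSS, SDS and SAS, the wording fits several variables, and no baseline adjustment is named for any of the four scales.

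All power figures are conditional on assumed inputs. Against unadjusted percentage change, the baseline-adjusted score gains about 2 to 27 points if the effect is additive, and may lose about 2 to 6 if effect and error are proportional to baseline. Most of the gain is due to the adjustment. The adjusted score is the safer choice: in simulation B it kept about 79–84% power in all 16 scenarios, while percentage change fell as low as 54%.

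The consequence is small. This is one of four secondary outcomes in a trial that calls itself exploratory, and the sample size does not depend on it.

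**What to change.** Define the outcome as the TCM syndrome total score (0 to 26), compared between arms at 6 months with the baseline score as covariate. This can be the 6-month contrast in the planned repeated-measures or GEE model, with months 1 to 6 as the outcomes and baseline moved to the covariates. Apply the same adjustment to CMSS, SDS and SAS, so that all four scales are handled alike. If a percentage reduction or responder share is wanted by convention, report it as supportive, with the formula or cut-off stated before unblinding.

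The cost is a sentence in the outcome definition and one in the Data analysis section. It needs no new data, visits or participants. The one downside is a less direct comparison with studies that report percentage reduction, which the supportive analysis largely covers.

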### Assessment of safety

All unexpected or unfavorable events affecting patients in the study, such as heavy menstrual flow, nausea, bloating, diarrhea, and stomach upset, associated with treatment [18, 19], will be recorded in detail in the CRFs and followed up for the duration of the study. Investigators will confirm the relatedness of adverse events and treatment and report treatment-related adverse events. In case of adverse reactions, the clinical observer can decide whether to stop the trial depending on the patient’s condition. In the event of any serious adverse events (SAEs), emergency medical assistance will be sought. The outcome will be assessed at 1, 2, and 3 months after randomization.

### Sample size

The sample size estimation was based on the mean difference in the change of the menstrual pain intensity from baseline. Based on previous studies and our pilot trial, we made the following assumptions in calculating the sample size: a mean difference of 1 between two groups, SD of total score of 1.67, a ratio of 1:1 between the two groups, a two-sided significance level of 0.025 and a power of 0.9 [35, 36]. With these assumptions, a minimum sample size of 116 patients (58 patients in each group) is needed. Considering an estimated 10% dropout rate, the estimated sample size was 128 patients (64 patients per group).

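### The stated 58 per group does not give 90% power at two-sided 0.025; it fits two-sided 0.05, the level used in the analysis section

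*Protocol article*

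**What the plan says.** The Sample size section bases the calculation on the between-group difference in change in menstrual pain. It assumes "a mean difference of 1 between two groups", "SD of total score of 1.67", "a ratio of 1:1 between the two groups", and "a two-sided significance level of 0.025 and a power of 0.9". From these it concludes that "a minimum sample size of 116 patients (58 patients in each group) is needed". It then allows for 10% dropout and arrives at 128 enrolled, 64 per group.

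The Data analysis section gives the only threshold for testing: "Statistical significance will be set at *P* < 0.05". It does not say whether the test is one- or two-sided; two-sided is the usual reading. The article does not link this level to the one used for sizing.

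**The concern.** Every input to the calculation is printed, so it can be repeated, and the printed answer does not follow from the printed inputs. A two-sided level of 0.025 is stricter than the usual 0.05 and needs a visibly larger trial than 58 per group.

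Two things are at stake. The first is the claim of 90% power at two-sided 0.025: if 0.025 is meant literally, the risk of missing a true effect of the assumed size is about 16 to 17% rather than 10%. The second is the reading of the result. The trial is sized at one level and tested at another, with no explanation. A primary P value between 0.025 and 0.05 would meet the analysis section's threshold but not the level used for planning.

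**Working it through.** **Inputs** (all from Sample size): difference d = 1; SD s = 1.67; 1:1 allocation; power 0.90; alpha 0.025, two-sided. Only the ratio d/s = 1/1.67 = 0.60 enters, so the units of the pain scale do not affect this check.

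**Formula** (two means, normal approximation): n per group = 2 × (z₁₋α/₂ + z₀.₉₀)² × s²/d², with 2 × 1.67² = 5.578 and z₀.₉₀ = 1.2816.

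**Step 1: find the level that reproduces 58.**

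- Two-sided 0.05 (the same critical value as one-sided 0.025): (1.9600 + 1.2816)² × 5.578 = 58.6. This matches the printed 58, apart from rounding down instead of up to 59. The t test needs 60.
- One-sided 0.05: 47.8, so 48. This does not match.

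**Step 2: use the level as written.**

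- Two-sided 0.025: (2.2414 + 1.2816)² × 5.578 = 69.2, so 70 per group and 140 in total. The t test needs 71 per group. The printed figures are 58 and 116.

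**Step 3: power at the planned sizes.** Power ≈ Φ(d / (s × √(2/n)) − z₁₋α/₂). At n = 58 the first term is √29 / 1.67 = 3.225. At two-sided 0.025 this gives Φ(3.225 − 2.241) = 83.7%; at two-sided 0.05 it gives Φ(3.225 − 1.960) = 89.7%.

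| n per group | Two-sided 0.025 | Two-sided 0.05 |
|---|---|---|
| 57.6 (64 less 10%) | 83.5% (normal) | 89.5% (normal) |
| 58 | 83.7% (normal), 82.8% (t) | 89.7% (normal), 89.2% (t) |
| 64 (no dropout) | 87.4% (normal), 86.7% (t) | 92.3% (normal), 91.9% (t) |

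At two-sided 0.025, no size up to full enrolment reaches 90%.

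**Step 4: dropout.** 116 / 0.9 = 128.9, so 129. The printed 128 is 116 × 1.1 = 127.6, rounded up. For 140 evaluable, 140 / 0.9 = 155.6, so 156.

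**Step 5: could a smaller variance explain 58 at two-sided 0.025?** That would need an SD of √(58/2) / (2.2414 + 1.2816) = 1.529. Since (1.529/1.67)² = 0.84, the variance would have to be about 16% lower than stated. The section mentions no gain from repeated measures or baseline adjustment.

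**The case against.** The strongest reply is that 0.025 was meant as the area in each tail. The design is then an ordinary two-sided 0.05 design with 89 to 90% power, and the fault is one mislabelled phrase in a trial that calls itself exploratory. This is the most likely explanation, and on that reading the trial is not underpowered in any way that matters. It does not rescue the text: a two-sided level of 0.025 means a total of 0.025, and nothing in the article tells the reader to take it otherwise.

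It can also be said that the Data analysis section alone sets a decision rule, so a P value between 0.025 and 0.05 would count as significant under the plan. That is fair. The article nowhere calls such a result a failure; the conflict is between the planning level and the testing level. But the mismatch is unexplained and should be settled in advance.

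A stricter level could have been chosen to allow for several endpoints or interim looks. The article names one primary outcome and describes no division of alpha. On interim analyses it disagrees with itself: Data analysis says none of outcomes is planned, while Oversight and monitoring says they will be performed. Even if 0.025 were such an adjustment, 58 per group would still be too few for it.

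The power after dropout describes completers. The full analysis set, with missing values carried forward, nominally keeps 64 per group. Carried-forward values add no real information, and 64 per group still falls short of 90% at two-sided 0.025.

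The rounding of 58.6 and the dropout shortcut are minor. Going from 59 to 58 per group changes power from 90.2% to 89.7% at two-sided 0.05, and the dropout step differs by one patient.

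**Conclusion.** The concern holds. With the article's own inputs, 90% power at two-sided 0.025 needs 140 evaluable patients, not 116: a shortfall of 24. At 58 per group the power at that level is about 83 to 84%. The printed size fits two-sided 0.05, where power is about 89 to 90%, and that is also the level in Data analysis if the test there is two-sided.

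This rests on a plain two-sample comparison of means with the stated difference and SD; the normal approximation and the t test agree to within about one percentage point. That one-sided 0.025 was mislabelled as two-sided is an inference, which the article does not confirm. If it is right, the error is a false design statement and a mismatch in alpha, not an undersized trial. If two-sided 0.025 was really intended, the trial is too small for its stated power.

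**What to change.** The sponsor should confirm which level was intended, without sight of unblinded outcome data, and make the two sections agree. Trial status says recruitment was under way at submission.

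- **If two-sided 0.05 was intended (recommended on the evidence of the figures):** in Sample size, give the level as two-sided 0.05 (one-sided 0.025), keep 128 enrolled, and state the power as about 89% after 10% dropout. In Data analysis, add that the 0.05 threshold is two-sided. This is a change of wording and needs no extra patients. Holding to a full 90% would mean 59 per group, 118 evaluable; 118 / 0.9 = 131.1, so 132 enrolled at 66 per group, 4 more than planned.
- **If two-sided 0.025 was intended:** change the threshold for the primary test in Data analysis to 0.025 and give the reason for the stricter level. Then either raise the size to 140 evaluable (about 156 enrolled, 28 more than planned), or keep 128 and state the power as about 83%.

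In either case, inflate for dropout by dividing by 0.9.

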### Data collection and management

This trial mainly involved randomized group data, baseline data, post-intervention outcome data, follow-up data, and statistical analysis result data. Randomized group data are provided and managed by the investigator responsible for the random grouping of the trial. Baseline data, post-intervention outcome data, and follow-up data are collected by dedicated data collection researchers. Statistical analysis result data are collected and provided by the researcher in charge of data statistical analysis. In order to maximize the completeness of data collection, we will enhance communication with patients. We will strengthen our contact with patients by phone or social media to remind and monitor their medications, in addition to the face-to-face reminders at each visit. Free examinations and treatments are offered during the study, and visit times are flexible according to the patient’s schedule as far as possible. Furthermore, we will hold regular TCM health lectures at our clinical trial center to engage participants. All participants are assessed at baseline and 1, 2, 3, 4, 5, and 6 months after randomization. Work training will be held before the start of the project to provide detailed training and explanation of the trial protocol, standard operating procedures (SOPs) for study operations, and the content of case report forms (CRFs). Well-trained assessors, blinded to the treatment assignment, will use CRFs to collect clinical data at each visit. The person in charge of CRFs checks the daily completion and files the case report form in summary after standardization. Supervisors also should randomly check the CRFs at any time. Data will be recorded on the paper version of CRFs by designated outcome assessors and double entered in the electronic CRFs. Any incomplete data will be recorded as unknown, missing, or not applicable. All study-related information, such as participants’ medical records, will be kept securely in locked file cabinets with limited access. All private subject data are encrypted and protected, visible only to the project’s principal investigators, and used only for the research of the project. Principal investigators will be granted access to the cleaned dataset. To ensure confidentiality, data dispersed to project team members will be kept confidential to any identifiable participant information.

